## 7.5. Risk-Benefit Considerations

The **risks** of the subretinal vector injection are related to 1) the surgical procedure three port pars plana vitrectomy and subretinal surgery as well as 2) the ophthalmic or systemic effects of the rAAV.hCNGA3 vector.

Regarding 1) there may be a potential loss of visual function due to complications of the surgical procedure such as bacterial infection, retinal detachment, suprachoroidal and/or subretinal hemorrhage and cataract as a consequence of the surgical trauma. These risks are treatable by standard ophthalmological care but may result in lack of partial or complete restoration of the visual function loss.

Table 2 gives an overview of known risks by pars plana vitrectomy based on the literature and experiences from NHP trials with the vector of this study and estimates the rates to be expected in the current trial. In case of the occurrence of any AE/complication listed in table 2, these will be treated according to standard of ophthalmological care.

| Surgical complications during 23g PPV | Overall rate with mixed indications  | Incidence in NHP study | Predicted risk in gene therapy trial |
|----------------------------------------------|----------------------------------------------------|------------------------|--------------------------------------|
| retinal detachment / breaks                  | 1-10 %                                             | 0%                     | 1%                                   |
| endophthalmitis                              | 0.01-1 %                                           | 0%                     | 0.01-1 %                             |
| wound leakage / transient hypotony           | 5-20 %                                             | 100%                   | 5-20 %                               |
| choroidal hemorrhage / detachment            | < 1 %                                              | 0%                     | < 1 %                                |
| suprachoroidal perfusion                     | < 1 %                                              | 0%                     | < 1 %                                |
| vitreal hemorrhage                           | 1-5%                                               | 0%                     | < 1 %                                |
| cataract formation                           | 1-5%                                               | 9%                     | 10-20%                               |
| transient intraocular hypertension           | 5%                                                 | 0%                     | 5%                                   |
| corneal erosion                              | 5-20 %                                             | 5-20 %                 | 5-20 %                               |

**Table 2:** Risks of complications during 23g PPV referring to literature, previous NHP studies and expected rates for the planned trial. [1] Wilkinson et al., 2013 [2] Lee et al., 2012 [3] Wykoff et al., 2010.

Regarding 2) there is a risk for a loss of vision due to ophthalmic immune reactions to the vector (indirect) or due to direct effects of the vector (however, pre-clinical

[figure not shown]

studies showed no toxic effects with up to 10 fold higher concentrations). If any immune reaction should be triggered by the vector, this might include non-infectious inflammation of the pigment epithelium (epitheliitis), retina (retinitis), vitreous cavity (vitritis) or uveal tissue (uveitis). None of these have been reported in any previous clinical trial involving AAV in ocular gene transfer.

Such effects may result in a significant deterioration of visual function (decrease in VA of  $\geq 15$  letters) and might also occur after initial improvement. A vulnerable period for direct and/or indirect (immunogenic) effects due to the viral packaging protein of the vector would be the first two weeks (time of concomitant steroid treatment). No clinical trial has as of yet reported immune-reaction to the transgene (even in systemic gene transfer). It therefore seems unlikely that a direct or indirect effect due to transgene expression would occur after ocular gene transfer in the immune-privileged subretinal space.

Previous clinical trials with the same viral vector build have demonstrated good safety profiles (Nathwani et al., 2011). Other trials have shown good safety profiles after subretinal application of similar viral vector constructs (rAAV2) (Bainbridge et al., 2008; Hauswirth et al., 2008; Maguire et al., 2008; Maguire et al., 2009; Bennett et al., 2012; Jacobson et al., 2012). However, systemic risks cannot be completely ruled out and could stem from - previously undetected - **immune reactions**. Both the virus capsid and transgenic protein could potentially activate the immune system. The immune-privilege of the eye severely limits the likelihood of antigen presentation to leukocytes. The compartmentalization of the eye limits the biodistribution of viral vector. Much lower doses are required in the eye compared to previous studies targeting the liver (Nathwani et al., 2011). The transgenic protein is not secreted but expressed intracellularly and only in target cells (cone photoreceptors) due to a cone photoreceptor specific promoter. In light of these arguments and supported by results from previous clinical trials, it seems unlikely that a significant immune reaction is staged after intervention. Nevertheless, as immune reactions cannot be ruled out completely, patients will be screened accordingly during the follow-up clinical examinations. Any systemic reactions may appear during the first days as headache and fever. For safety reasons, patients will be hospitalized for three days including monitoring over the first night. Blood pressure, pulse and body temperature will be measured every 4 hours on day 1 post-op. These parameters will be measured twice at day 2 post-op. For hygiene procedure see 7.6.

The potential of **malignancy** due to the AAV vector is also very unlikely. In contrast to e.g. lentiviral vectors, rAAV are considered non-integrating and result in episome formation in the transduced cells rather than integrating the transgene cassette in the host genome. Wild-type AAVs carry the complete virus genome including re *Rep* genes, which orchestrate the integration of vector DNA (preferentially at the AAVS1 locus (c19q13.3)). Deletion of AAV *Rep* in the recombinant vector reduces these integration events by more than 99.5% (Schnepp et al., 2003). So far, there has been no report on insertional mutagenesis of recombinant AAV (Lipinski et al., 2013).

[figure not shown]

Nevertheless, all patients in this trial will be screened regularly even after study close out.

Subjects will be encouraged to monitor themselves and to assist in reporting adverse events; they will be provided with laminated wallet-sized cards with investigator contact information. Additionally, health care professionals treating the study patients, who are not otherwise associated with the clinical trial, will be notified to provide prompt reports of adverse events to the investigators. Investigators will maintain in the case history records of exposures to mutagenic agents and other medicinal products along with subjects' adverse event profiles. Clinical information will focus on information pertaining to new malignancies, new incidence or exacerbation of a pre-existing neurological disorder, new incidence or exacerbation of a prior rheumatologic or other autoimmune disorder, and new incidence of a hematologic disorder. For the subsequent years, subjects will be contacted at a minimum of once per year. A clinical questionnaire, administered by telephone call or at the eye hospital Tübingen or at the subject's home ophthalmological treatment centre, will focus on information pertaining to new malignancies, new incidence or exacerbation of a pre-existing neurological disorder, and new incidence or exacerbation of visual disturbances. It will ask subjects to describe any adverse events, including any unexpected illness and/or hospitalization, and provide a description of exposures to mutagenic agents and other medicinal products.

Dissemination of rAAV.hCNGA3 would most likely only occur between human beings, since it is derived from AAV2/8. However no replication is expected in normal cells of treated individuals exposed to the replication-deficient virus, or from exposure of uninfected people to treated individuals.

**Germline transmission** is theoretically possible but requires biodistribution far beyond what could be detected today combined with the extremely unlikely event of genomic integration.

Currently, there is no experience with the specific **teratogenicity** of the rAAV.hCNGA3 vector, therefore the risk for an unborn child in case of an unforeseen conception, especially during the first half of the study participation, cannot be judged.

Generally, there is the potential of no subjective or objective benefit despite the risks of the procedure.

Patient **benefits** may consist in a deceleration or even halt of cone photoreceptor degeneration and in the initiation of cone photoreceptor function. This might include improvement of visual acuity, decreased glare, increased ability of color discrimination and decreased nystagmus. Especially the debilitating glare is a major impairment in achromatopsia patients' daily life. In addition, many patients are hampered by their very low vision. Beyond glare and visual acuity, novel colour perceptions may be an individual gain for the patients and their performance in daily

[figure not shown]

life. Improvements in visual functions are known to increase the vision-related quality of life and general well-being.

## **7.6. Risks for the Environment**

These are dealt with in detail in the separate document *Information required concerning releases of genetically modified organisms* according to Annex IIIa of the DIRECTIVE 2001/18/EC OF THE EUROPEAN PARLIAMENT AND OF THE COUNCIL of 12 March 2001 on the deliberate release into the environment of genetically modified organisms and repealing Council Directive 90/220/EEC.

Dissemination of rAAV.hCNGA3 would most likely only occur between human beings, since it is derived from AAV2/8. However no replication is expected in normal cells of treated individuals exposed to the replication-deficient virus, or from exposure of uninfected people to treated individuals.

Safety countermeasures will be taken for the clinical phase I trial with regard to the results mentioned above. Until day 7 post-injection, any materials and tissues coming into contact with the patient's eyes, lachrymal fluid and nasal secretions will be collected in designated collecting boxes and will be subject to disinfection or autoclaving respectively (for more details see SOP waste treatment). After hospitalization patients will get collecting boxes to collect the materials mentioned above also in the hotel or at home. The boxes will be collected by the study team for destruction. Study patients will be instructed to not manipulate the eye after surgery to facilitate rapid closure of the self-sealing sclerotomies. Study patients will also be instructed to avoid intimate physical contact to other subjects until day 7 post-injection (See also section 1.3.3.).

## **8. Examinations**

All study visits described in the flowchart, page 14, and in section 8.1. may be performed on two consecutive days; screening and close-out visit on three days if deemed necessary. The reason behind this is to reduce the workload due to concentration during test procedures and to improve the reliability of the test results.

### **8.1. Screening Examinations**

(O) = optional, if control deemed necessary by investigator

#### **Visit 1**

##### **Screening (Day -30 to -2)**

- Medical/surgical history
- Ocular/surgical history
- BMI
- Vital Signs
- Urine pregnancy test

[figure not shown]

- 4168 - Hematology/basic chemistry/urine analysis
- 4169 - CRP, IgG, IgM
- 4170 - Immunopathology
- 4171 - PCR of rAAV8 genome
- 4172 - Best corrected visual acuity
- 4173 - Basic ophthalmological exam (miosis)
- 4174 - Contrast sensitivity (PR Charts)
- 4175 - Flicker Fusion Frequency
- 4176 - Colour constancy (chromatic adaption)
- 4177 - Anomaloscopy
- 4178 - Cambridge Colour Test / Farnsworth D15
- 4179 - IR Video Pupillography
- 4180 - MP-1 Microperimetry (20°)
- 4181 - Funduscopy (mydriasis)
- 4182 - Dark adaption test
- 4183 - ffERG (scotopic and photopic)
- 4184 - sd-OCT
- 4185 - Fundus autofluorescence
- 4186 - Fundus photography
- 4187 - Angiography
- 4188 - Systemic steroids (Day -1)
- 4189 - Topical steroids and antibiotics (Day -1)
- 4190 - VFQ25
- 4191 - Psychiatric examination
- 4192 - Brief Symptom Inventory (BSI)
- 4193 - Concomitant medication
- 4194 - HIV Test
- 4195

## 4196 ***8.2. Trial Examinations***

### 4197 **Visit 2**

#### 4198 **DO**

- 4199 - Vital signs
- 4200 - Urine pregnancy test
- 4201 - Hematology/ basic chemistry (O)
- 4202 - Basic ophthalmological exam (miosis)
- 4203 - Funduscopy
- 4204 - sdOCT (O)
- 4205 - Systemic steroids
- 4206 - Topical steroids and antibiotics
- 4207 - Subretinal injection of rAAV8 vector
- 4208 - Psychological counselling
- 4209 - Adverse event recording
- 4210 - Concomitant medication
- 4211
- 4212
- 4213

[figure not shown]

4214  
4215  
4216  
4217  
4218  
4219  
4220  
4221  
4222  
4223  
4224  
4225  
4226  
4227  
4228  
4229  
4230  
4231  
4232  
4233  
4234  
4235  
4236  
4237  
4238  
4239  
4240  
4241  
4242  
4243  
4244  
4245  
4246  
4247  
4248  
4249  
4250  
4251  
4252  
4253  
4254  
4255  
4256  
4257  
4258  
4259

**Visit 3****D1**

- Vital signs (O)
- Hematology/ basic chemistry (O)
- Basic ophthalmological exam (miosis)
- Funduscopy (mydriasis)
- sdOCT (O)
- Systemic steroids
- Topical steroids and antibiotics
- Psychological counselling
- Adverse event recording
- Concomitant medication

**Visit 4****D2**

- Vital signs (O)
- Hematology/ basic chemistry (O)
- CRP, IgG, IgM
- Basic ophthalmological exam
- Funduscopy (mydriasis)
- sdOCT (O)
- Systemic steroids
- Topical steroids and antibiotics
- Psychological counselling
- Adverse event recording
- Concomitant medication

**Visit 5****D3 (± 1 Day)**

- Vital signs
- Hematology/ basic chemistry
- CRP, IgG, IgM
- PCR of rAAV8 genome
- Basic ophthalmological exam (miosis)
- Funduscopy (mydriasis)
- Contrast sensitivity (PR charts)
- sdOCT (O)
- Systemic steroids
- Topical steroids and antibiotics
- Psychological counselling
- Adverse event recording
- Concomitant medication

[figure not shown]**Visit 6****D14 ( $\pm$  3 days)**

- Vital signs (O)
- Urine pregnancy test
- Hematology/ basic chemistry
- CRP, IgG, IgM
- PCR of rAAV8 genome
- Basic ophthalmological exam (miosis)
- Visual Acuity, BCVA (ETDRS)
- Contrast sensitivity (PR charts)
- Anomaloscopy
- Cambridge Colour Test / Farnsworth D15
- Funduscopy
- sdOCT
- FAF
- FF
- Angiography (O)
- Anomaloscopy
- Roth 28-hue test (sat. and de-sat.)
- IR-Video-Pupillography
- MP-1 Microperimetry (20°)
- Dark adaptation test (FST)
- Topical steroids and antibiotics
- Brief Symptom Inventory (BSI)
- Psychological counselling
- Study specific scale, A3-PRO
- Adverse event recording
- Concomitant medication

**Visit 7****D30 ( $\pm$  5 days)**

- Vital signs (O)
- Urine pregnancy test
- Hematology/ basic chemistry (O)
- CRP, IgG, IgM
- Immunopathology
- PCR of rAAV8 genome (O)
- Visual Acuity, BCVA (ETDRS)
- Basic ophthalmological exam (miosis)
- Contrast sensitivity (PR charts)
- Flicker Fusion Frequency
- Colour Constancy (chromatic adaption) (O)
- Anomaloscopy
- Cambridge Colour Test / Farnsworth D15
- IR Video Pupillography

[figure not shown]

- 4306 - MP-1 Microperimetry (20°)
- 4307 - Funduscopy (mydriasis)
- 4308 - Dark adaptation test
- 4309 - ff-ERG (scotopic and photopic)
- 4310 - sdOCT
- 4311 - FAF
- 4312 - FF
- 4313 - Angiography (O)
- 4314 - Topical steroids and antibiotics
- 4315 - VFQ25
- 4316 - Brief Symptom Inventory (BSI)
- 4317 - Psychological counselling
- 4318 - Study specific scale, A3-PRO
- 4319 - Adverse event recording
- 4320 - Concomitant Medication
- 4321
- 4322

## Visit 8

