## **3. Study Plan**

### **3.1. Study Design**

This is an open mono-center trial with fellow-eye comparison. Three patients will be assigned to three consecutive, increasing dosage groups (see figure 3):

4) low dose:  $\leq 1 \times 10^{10}$  vgp (n=3)

Between each injection (between patient 1 and 2 and patient 2 and 3) a safety interval of 4 weeks will be kept.

After collection of data on study visit Day 30 of all three patients of the dose cohort and before the scheduled start of the next injections of the consecutive dosage group the DMC will meet and evaluate safety data. If no safety concerns are reported the next dosage group of patients will be treated as scheduled. DMC advice may also result in a dose reduction for the next dosage cohort.

5) intermediate dose:  $\leq 5 \times 10^{10}$  vgp (n=3)

Between each injection (between patient 4 and 5 and patient 5 and 6) a safety interval of 4 weeks will be kept.

After collection of data on study visit Day 30 and before the scheduled start of the next injections of the consecutive dosage group the DMC will meet and evaluate safety data of groups 1 and 2. If no safety concerns are reported the next dosage group of patients will be treated as scheduled. DMC advice may also result in a dose reduction for the next dosage cohort. Within the high dose cohort, the interval between injections / individual patients will be four weeks.

6) high dose:  $\leq 1 \times 10^{11}$  vgp (n=3)

Between each injection (between patient 7 and 8 and patient 8 and 9) a safety interval of 4 weeks will be kept.

The following figure (Fig. 3) explains the schedule and timelines of dose groups and the points of decisions of the data monitoring committee.

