### 7.2. Safety

#### 7.2.1. Ocular and systemic safety

**Safety** as primary endpoint will be assessed by clinical examination of  
*Ocular safety*

3. loss of  $\geq 15$  letters visual acuity at 1m
4. severe, vector-induced, intraocular inflammation unresponsive to treatment

*Systemic safety*

5. vital signs
6. routine clinical chemistry testing (including CRP, IgG, IgM and full/differential blood counts)
7. Immunopathology essays will include specific enzyme-linked immunosorbent assays for humoral antibodies against rAAV8 capsid protein
8. Biodistribution will be monitored by polymerase chain reaction studies on rAAV2/8 genome in blood, urine, saliva and lachrymal fluid.

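### At the D30 visit that gates each dose escalation, vital signs, blood count/chemistry and vector PCR are optional, so the DMC may have no required values later than D3 or D14 for them

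*Supplement*

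**What the plan says.** All references are to protocol version 5.0.

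**The gate.** Section 3.1 has the DMC meet "After collection of data on study visit Day 30 of all three patients of the dose cohort" and before the next dose group is injected. The same Day 30 trigger applies after the second cohort. Section 7.3.1 repeats that the go/no-go decision follows each patient's Day 30 results.

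**The endpoint.** Section 7.2.1 gives four systemic components of the primary safety endpoint: vital signs; "routine clinical chemistry testing (including CRP, IgG, IgM and full/differential blood counts"); antibodies against the capsid; and biodistribution by PCR.

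**The schedule.** At Visit 7 (D30) section 8.2 lists "Hematology/ basic chemistry (O" and "PCR of rAAV8 genome (O", and marks vital signs in the same way. Section 8.1 defines the mark as "optional, if control deemed necessary by investigator". Flowchart rows 4, 6 and 9 carry the matching o at D30. CRP/IgG/IgM and "Immunopathology" (the capsid ELISA) carry no such mark and are required.

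**A separate mismatch.** Section 8.2, Visits 3 and 4, marks vital signs optional at D1 and D2. The flowchart marks them x on both days. Section 7.5 says "Blood pressure, pulse and body temperature will be measured every 4 hours on day 1 post-op", with two measurements on day 2.

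**The concern.** The plan ties escalation to one visit and then leaves three of that visit's systemic measurements to discretion. No section lists which systemic results the DMC must have before it decides.

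Recency matters here because of two statements in the plan itself. Section 8.4.27 keeps patients on systemic steroids from day -1 and tapers them only after day 19. Section 7.2.3 considers toxic effects of the transgene product, which might include immune reactions, unlikely to show before about two weeks after surgery. The earlier required samples therefore come from a period when a systemic signal is either not yet expected or may be masked by steroids. D30 is the first scheduled visit outside that period, and two escalation decisions covering six patients (cohorts 1 and 2, three each) rest on it.

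**Working it through.** No sample size, power or error rate is involved. The check is a count of schedule entries and a calculation of gaps.

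**Step 1. Required systemic measurements after dosing, up to D30** (section 8.2 Visits 3 to 7; flowchart rows 4, 6, 7, 8, 9):

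| Procedure | Required after dosing | At D30 |
|---|---|---|
| Vital signs | D3 (flowchart: D1, D2, D3) | optional |
| Haematology/basic chemistry | D3, D14 | optional |
| CRP, IgG, IgM | D2, D3, D14, D30 | required |
| Capsid ELISA | D30 | required |
| Vector PCR | D3, D14 | optional |

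At D30, 3 of 5 procedures are optional and 2 of 5 required. Set against the four components of 7.2.1, vital signs and PCR are optional, the antibody assay is required, and clinical chemistry is split: CRP and immunoglobulins required, blood count and the rest of the panel optional. Over the whole period to D30, all 5 have at least one required measurement after dosing.

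**Step 2. Age of the last required value at the patient's own D30 visit.** Visit windows are D3 ± 1, D14 ± 3 and D30 ± 5 days.

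- Blood count/chemistry and PCR: 30 − 14 = 16 days. Shortest: 25 − 17 = 8. Longest: 35 − 11 = 24.
- Vital signs: 30 − 3 = 27 days. Shortest: 25 − 4 = 21. Longest: 35 − 2 = 33.

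The DMC meets after the third patient's D30 visit, so values for the first two patients in a cohort are older still by then. The next scheduled visit, D90, also marks all three procedures optional.

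**Step 3. Position relative to the steroid taper and the two-week point.** The latest D14 visit is 14 + 3 = day 17, always before day 19. The earliest D30 visit is 30 − 5 = day 25, always after it. The earliest D14 visit is 14 − 3 = day 11, which can precede the two-week point in 7.2.3. D3 always precedes it. So no required blood count, chemistry, PCR or vital sign before the gate is taken after the taper can begin.

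**Step 4. Stated reasons for the optional marks.** Section 8.4.9 says PCR is done at early visits and afterwards at the investigator's judgement, so late PCR is a stated choice, although that section does not mention the escalation gate. Sections 8.4.4 (vital signs) and 8.4.6 (haematology and chemistry) give no reason for leaving D30 optional.

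**The case against.** The strongest reply is that the DMC reviews the cohort's safety data as a whole (7.2.2), and every procedure has a required measurement after dosing before the decision. At D30 itself visual acuity, slit-lamp examination, funduscopy, OCT, ERG, CRP/IgG/IgM, the ELISA and adverse event recording are all required. This covers both ocular components of the primary endpoint. Serious adverse events reach the DMC within one day (7.3.1). The named stopping events in 7.4 are vision loss, ocular inflammation and SUSARs, none of them defined by a routine vital sign or PCR. All of this stands. A reader might infer that the DMC could decide without most systemic primary safety data, or that Day 30 safety data might not exist. The documents support neither. What the reply leaves open is timing: an abnormal laboratory value after the taper counts as an adverse event only if someone measures it.

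Two further inferences also fail.

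- Section 1.3.3 reports vector DNA in primate blood up to four weeks, which might seem to show that D14 is too early for the last PCR. That finding is from the intravitreal high-dose group. By Appendix 1 the high dose was 1×10^12 vgp, ten times the trial maximum of 1×10^11, and 100 and 20 times the ceilings of cohorts 1 and 2 (1×10^10 and 5×10^10). None of the 12 subretinally injected animals had detectable DNA in blood at 72 hours. Persistence of that kind would also be expected to show in the required D3 and D14 samples.
- Values taken only when the investigator sees a need are a selected set, so their means would mislead. But section 10.4 does not name laboratory values, vital signs or PCR among the measurements to be averaged.

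The D1/D2 mismatch is a documentation fault and adds nothing to the weight of the D30 point.

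**Conclusion.** The point holds as a gap in recency at the decision visit. Three of five systemic procedures are optional at D30. The DMC may decide with no blood count, chemistry or PCR later than D14 (16 days; 8 to 24) and no vital signs later than D3 (27 days; 21 to 33), all taken before the steroid taper begins. The case is clear for vital signs and for haematology/chemistry, where no reason is given. It is weaker for PCR, where discretion is stated policy and only the link to the gate is missing.

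This is a worthwhile and inexpensive improvement to the safety review; it does not invalidate the escalation design. The sizes assume that visits fall within their windows and that the investigator does not use the option. If the tests were in fact done at D30, the gap did not arise in practice. Version 5.0 is dated 16 February 2017, after the planned last first visit of November 2016, so the escalation decisions may already have been taken. The documents do not say.

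**What to change.** 1. In the flowchart, change o to x at D30 for vital signs (row 4) and haematology/basic chemistry (row 6), and remove the (O) from both in section 8.2, Visit 7.
2. For PCR, either require the D30 sample in cohorts 1 and 2, or state in section 3.1 or 7.3.1 that the DMC relies on the D14 result.
3. Separately, reconcile the D1 and D2 vital-signs entries in section 8.2, Visits 3 and 4, with the flowchart and section 7.5.
4. If both escalations have already taken place, report for each of the six patients in cohorts 1 and 2 which of the three tests were done at D30 and were before the DMC.

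The cost is small: a seated vital-signs reading and a few extra assays on blood already drawn at D30 for CRP/Ig and the ELISA, in nine patients. A D30 PCR would cost somewhat more, since 7.2.1 also names urine, saliva and lachrymal fluid. Stating reliance on D14 costs only a sentence.
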